## Abstract

**Background:**

Meaning-focused coping may be at the core of adequate adjustment to life after cancer. Cancer survivors who experience their life as meaningful are better adjusted, have better quality of life and psychological functioning. Meaning-Centered Group Psychotherapy for Cancer Survivors (MCGP-CS) was designed to help patients to sustain or enhance a sense of meaning and purpose in their lives. The aim of the proposed study is to evaluate the effectiveness and cost-effectiveness of MCGP-CS.

**Methods/Design:**

Survivors diagnosed with cancer in the last 5 years and treated with curative intent, are recruited via several hospitals in the Netherlands. After screening, 168 survivors are randomly assigned to one of the three study arms: 1. Meaning-Centered Group Psychotherapy (MCGP-CS) 2. Supportive group psychotherapy (SGP) 3. Care as usual (CAU). Baseline assessment takes place before randomisation, with follow up assessments post-intervention and at 3, 6 and 12 months follow-up. Primary outcome is meaning making (PMP, PTGI, SPWB). Secondary outcome measures address quality of life (EORTC-30), anxiety and depression (HADS), hopelessness (BHS), optimism (LOT-R), adjustment to cancer (MAC), and costs (TIC-P, EQ-5D, PRODISQ).

**Discussion:**

Meaning-focused coping is key to adjustment to life after cancer, however, there is a lack of evidence based psychological interventions in this area. Many cancer survivors experience feelings of loneliness and alienation, and have a need for peer support, therefore a group method in particular, can be beneficial for sustaining or enhancing a sense of meaning. If this MCGP-CS is effective for cancer survivors, it can be implemented in the practice of psycho-oncology care.

**Trial registration:**

Netherlands Trial Register, NTR3571

## Background

In the past decade, life expectancies of cancer patients have increased significantly. Due to recent innovations in early detection and treatment, many patients have become cancer survivors and the population of cancer survivors is growing [1,2].

Many cancer patients seem to experience the diagnosis of cancer as a challenge to experiencing life as meaningful, for instance due to shifted priorities in life, or physical hindrances in achieving goals. For some people, the diagnosis of cancer can lead to the experience of life with little or no meaning [3]. Meaning in life is strongly associated to psychological well-being and is liable to alteration after a negative experience like cancer [4-6]. Meaning-focused coping may be at the core of adequate adjustment to cancer: cancer patients who experience their life as meaningful are better adjusted, have better quality of life and psychological functioning [4,7]. Therefore, a meaning-focused psychological intervention might be beneficial for cancer survivors to increase adequate adjustment to life after cancer and prevent and decrease psychological distress.

Several interventions for cancer patients focusing at least partly on experiencing meaning in life have been developed and evaluated. The outcomes of several evaluation studies are promising with improved self esteem, optimism, mood, sense of meaning, spiritual well-being and decreased suffering after intervention. These studies are, however, hampered by methodological limitations, like high dropout rates, no control for the effects of attention, insufficient information on the treatment protocol and short periods of follow up [8-17]. Most of the studied interventions target cancer patients in the palliative phase. None of the described studies assess the cost-effectiveness. To our knowledge there are no randomized controlled trials on meaning-centered psychological interventions targeting cancer survivors.

In the proposed study, we aim to evaluate the effectiveness of a newly developed meaning-centered group psychotherapy for cancer survivors, based on the Meaning-Centered Group Psychotherapy (MCGP) [18]. MCGP, developed by Breitbart and colleagues, is grounded in Frankl’s work and was designed to help patients with advanced cancer to sustain or enhance a sense of meaning, peace and purpose in their lives, despite the confrontation with death [18]. Frankl stated that the will to meaning is the primary motivation of humans [19-21]. He developed a meaning-centered approach in psychotherapy, called *logotherapy*, that focuses on assisting people to detect their individual meaning or purpose in life. A pilot randomized controlled trial showed that MCGP is potentially beneficial for advanced cancer patients for decreasing emotional and spiritual suffering [11].

In the present study, we adapted MCGP for cancer *survivors* (MCGP-CS). Based on outcome of a focus group study on 23 patients [22], and on the input of two psychotherapists with expertise in this specific area, we adjusted the MCGP manual to make it compliant for cancer survivors. Through this focus group study we obtained insight in how survivors experience and talk about meaning in life, and in their perceived need for help with meaning making. In addition, the results indicated that some cancer survivors succeeded in meaning making efforts and experienced sometimes even more meaning in life than before diagnosis, while others struggled with meaning making and expressed an unmet need for help [22]. In preparation of the randomized controlled trial (RCT) studying effectiveness, the feasibility of the MCGP-CS protocol was tested in a feasibility study among 11 participants, divided over two groups. The outcomes of the feasibility study were positive: patient satisfaction and compliance were high [23].

Based on the results of these studies, the MCGP-CS manual and protocol were finalized. An example of an adjustment to Breitbart’s original MCGP for palliative patients addresses attitudinal sources of meaning. In the advanced cancer patient protocol, patients are asked to respond to questions like ‘What would you consider a good or meaningful death?’ ‘How can you imagine being remembered by your loved ones?’ In the adjusted protocol for cancer survivors, they are asked to respond to questions like ‘What are limitations in your life at the moment?’ ‘How can you carry on in life, despite these limitations?’ ‘What do you want to do *now*, that will make you happy and satisfied when you to die later?’ Another change that has been made, based on expert advices, is that every experiential exercise starts with a brief meditation exercise, so feelings can be processed at a deeper level.

The main goal of the present study is to assess effectiveness and cost-effectiveness of MCGP-CS, compared to supportive group psychotherapy (SGP) and to care as usual (CAU) among cancer survivors with psychological or existential distress after treatment and a need for help.

## Methods/Design

### Design

This study is a prospective randomized controlled trial with three study arms: MCGP-CS, SGP and CAU. Cancer survivors are recruited in two different ways: via several hospitals in the Netherlands (region Leiden and Amsterdam) and via public media (i.e. advertisement on websites of patient societies, and in magazines and local newspapers). All cancer survivors who meet in- and exclusion criteria are asked to participate. Survivors are assigned through cluster randomisation to one of the three study arms. The baseline assessment takes place before randomisation, with follow up assessments one week post-intervention and at 3, 6 and 12 months follow-up. Reasons for dropout are registered. The study protocol, information brochure, questionnaires and informed consent form are approved as a multicenter study by the Medical Ethics Committee of the Leiden University Medical Center. The design is illustrated in Figure 1.

**Figure 1 F1:**
[figure not shown]
Design of the RCT.

### Study sample

*Inclusion criteria:* cancer diagnosis in the last 5 years, treated with curative intent, main treatment is completed (i.e. surgery, radiotherapy, chemotherapy), ability to attend all therapy sessions, expressed need for psychological help/support and at least one psychosocial complaint (e.g. depressed mood, anxiety, coping issues, life questions, meaning making problems, relationship problems).

*Exclusion criteria:* severe cognitive impairment, current psychological treatment and insufficient mastery of Dutch language.

The criteria are ascertained during a telephonic interview by a trained psychologist.

A study specific questionnaire comprises questions about sociodemographic (age, gender, religious background, marital status, family situation, education level, other important life events in the past 2 years) and clinical characteristics (type of cancer, cancer treatment, time since treatment) and will be filled out by participants at the first assessment, at baseline. Participants are asked which study-condition has their preference; this will not influence the assignment to the conditions.

### Randomization

Cancer survivors who meet the inclusion criteria and sign the informed consent, are allocated to a group. When the group counts 8 survivors, the group is randomly assigned by an independent researcher, through blocked randomization with randomly selected block sizes, to one of the three study arms.

### Meaning-centered group psychotherapy targeting cancer survivors (MCGP-CS)

Cancer survivors in the experimental study arm participate in MCGP-CS. The main purpose of the MCGP-CS is to sustain or enhance a sense of meaning or purpose in the patient’s life, in order to cope better with the consequences of cancer. MCGP-CS is a manualized 8-week intervention that makes us of didactics, group discussion and experiental exercises that focus around themes related to meaning and cancer survivorship. The sessions take two hours each and are held weekly. The participants use a workbook (called *Life lessons portfolio*) and get homework assignments every week. MCGP-CS is led by one psychotherapist with experience in treating patients with cancer. Each session addresses a specific theme that is related to the concepts and sources of meaning. The themes of the sessions are: 1. Concept and sources of meaning, 2. Meaning before and after cancer, 3. The story of our life as a source of meaning: what made us who we are today, 4. The story of our life as a source of meaning: things we have done and want to do in the future, 5. Attitudinal sources of meaning: encountering life’s limitations, 6. Creative sources of meaning: responsibility, courage and creativity, 7. Experiental sources of meaning, 8. Termination: presentations of our life lessons and goodbyes. Table 1 gives an overview of the themes of each session.

**Table 1 T1:** **Session topics covered in MCGP-CS**^
**1 **
^**and SGP**^
**2**
^

**Session**	**MCGP-CS**	**SGP**
1	Concept and sources of meaning	Group member introductions
2	Meaning before and after cancer	The need for support
3	The story of our life as a source of meaning: what made us who we are today	Coping with the medical test and communicating with providers
4	The story of our life as a source of meaning: things we have done and want to do in the future	Coping with family and friends
5	Attitudinal sources of meaning: encountering life’s limitations	Coping with vocational issues
6	Creative sources of meaning: responsibility, courage and creativity	Coping with body image and physical functioning
7	Experiental sources of meaning	Coping with the future
8	Termination: presentations of our life lessons and goodbyes	Termination: Goodbyes and how do we go from here?

^1^Meaning-Centered Group Psychotherapy for Cancer Survivors.

^2^Supportive Group Psychotherapy.

### Supportive group psychotherapy (SGP)

The control condition is an 8-week social support group following Payne et al. [24]. The sessions take two hours and are held weekly. Each group is supervised by a psychotherapist with experience in treating patients with cancer. The psychotherapist has an unconditionally positive regard and empathetic understanding, stimulates patients to actively share their experiences, and focuses on positive emotions, and expression of feelings.

Each of the 8 sessions has a different theme, which is mentioned at the beginning of the session. The themes of the sessions are: 1. group members’ introductions, 2. need for support, 3. coping with medical tests and communicating with physicians, 4. coping with family and friends, 5. coping with work issues, 6. coping with body image and physical functioning, 7. coping with the future, 8. termination: where do we go from here? Table 1 gives an overview of the themes of each session.

### Care as usual (CAU)

Cancer survivors assigned to the CAU study arm do not participate in one of the group interventions. If a patient in the CAU study arm asks the researcher for psychological help, he or she is referred to their General Practitioner (GP). Health care uptake is closely monitored, to enable detailed post-hoc description of what CAU entailed exactly.

### Treatment quality

In the MCGP-CS and the SGP study arms, after each session, the psychotherapist writes a short summary of the session where he/she notes whether the protocol was followed. All group sessions are audio taped and randomly selected audio fragments will be analysed by the researchers to establish whether the therapy protocol was followed correctly.

### Outcome assessment

Outcomes measures include questionnaires on meaning, quality of life, anxiety and depression, hopelessness, optimism, mental adjustment to cancer, satisfaction with the intervention, and sociodemographic and clinical characteristics. Furthermore, a cost-evaluation will be carried out. Patients can choose to complete questionnaires online or via pen and paper. Primary outcomes are collected at all time points (baseline, after one week, 3, 6, and 12 months). Secondary outcome measures are collected at baseline, after one week, 3 and 6 months. Cost evaluation outcomes are collected at baseline, after 3, 6, and 12 months). A complete overview of the outcome measures is presented in Table 2*.*

**Table 2 T2:** Outcome measures and instruments

**Outcome measures**	**Instrument**
*Primary*^ *1* ^	
Meaning	Personal Meaning Profile (PMP) [24]
Post Traumatic Growth	Post Traumatic Growth Inventory (PTGI) [25]
Positive psychological functioning and wellbeing	Ryff’s Scale of Psychological Well-being (SPWB) [26]
*Secondary*^ *2* ^	
Quality of life	30-item EORTC QLQ-C30 (version 3.0) [27,28]
Anxiety and Depression	Hospital Anxiety and Depression Scale (HADS) [29]
Hopelessness	Beck Hopelessness Scale (BHS) [30,31]
Optimism	Life Orientation Test (LOT-R) [31,32]
Adjustment to cancer	Mental Adjustment to Cancer (MAC) [20]
*Cost evaluation*^3^	Trimbos and iMTA questionnaire on Costs associated with Psychiatric illness (TiC-P) [34,35]
	EQ-5D [36]
	PRODISQ [37]

^1^Assessment at T0, T1, T2, T3, T4.

^2^Assessment at T0, T1, T2, and T3.

^3^Assessment at T0, T2, T3 and T4.

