### Cost-evaluation

Direct medical and direct non-medical cost data are collected with the Trimbos and iMTA questionnaire on Costs associated with Psychiatric illness (TiC-P) [35,36]. Unit resource use (GP visits, hospital days, etc.) will be multiplied by their appropriate integral cost prices.

An economic evaluation regarding work (loss) and health care use will be conducted as a cost-utility analysis for (changes in) health-related quality of life as assessed with the EQ-5D [37].

Indirect non-medical cost data related to production losses through work loss days and work cutback days will be sampled with the appropriate PRODISQ modules [38]. Indicators of return to work (RTW) are: Time to partial and to full RTW, meaning number of calendar days between end of treatment and first day at work; Time to full RTW corrected for partial RTW.

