### Statistical analyses

Descriptive statistics, t-tests and Chi^2^ tests will be used to determine whether patient characteristics are similar across experimental conditions. Results will be reported on an intention-to-treat basis. The Linear Mixed Modeling (LMM) procedure will be used to estimate missing values. This procedure includes incomplete cases in the analysis and employs restricted maximum likelihood estimation to calculate parameter estimates. LMM assumes that missing data are missing at random. LMM will be used to investigate the longitudinal development of meaning making in the three groups. The effect of study condition will be tested using contrasts within the LMM. Mediation analyses [39,40] will be used to test as whether development in the patients’ meaning making explains/mediates the expected improvement in psychological functioning in the MCGP condition.

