### Economic outcomes

For the economic evaluation we will make use of the pertinent guidelines [36,41-43]. The societal perspective will be taken encompassing intervention costs, direct non-medical costs and indirect costs. The latter is not expected to be very important in the studied population, which is characterised by unemployment, but the data on production losses will be collected anyway. Production losses will be economically valuated using the friction cost method [44]. Costs and effects will be analysed simultaneously, incremental cost-effectiveness ratios (ICERs) will be calculated and placed within 95% confidence intervals, 2,500 bootstrap replications of the ICERs will be projected on a cost-effectiveness plane, ICER acceptability curves will be plotted against different willingness-to-pay ceilings [45], and sensitivity analysis will be conducted as a matter of course focussing on uncertainty in the main cost-drivers. This will be done for the costs per QALY gained in a cost utility analysis.

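### EQ-5D is not measured at T1, so a short-lived utility change at the end of therapy goes unseen and the QALY difference may be biased in either direction

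*Protocol article*

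**What the plan says.** The Outcome assessment section of the protocol article states: "Cost evaluation outcomes are collected at baseline, after 3, 6, and 12 months". Footnote 3 of Table 2, which covers the TiC-P, EQ-5D and PRODISQ, agrees: "Assessment at T0, T2, T3 and T4". T1 is absent from both.

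The other instruments are collected at T1. Primary outcomes are taken at all five time points, and for the secondary set, which includes the QLQ-C30, the text reads "Secondary outcome measures are collected at baseline, after one week, 3 and 6 months".

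The Design section gives the timing as "follow up assessments one week post-intervention and at 3, 6 and 12 months follow-up". It does not say whether the months run from baseline or from the end of therapy. On duration, "MCGP-CS is a manualized 8-week intervention"; the supportive group therapy also lasts 8 weeks.

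The Cost-evaluation section plans a "cost-utility analysis for (changes in) health-related quality of life as assessed with the EQ-5D". The Economic outcomes section, after describing ICERs, bootstrap replications and acceptability curves, adds: "This will be done for the costs per QALY gained in a cost utility analysis". Neither section says how utility is to be interpolated between visits.

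**The concern.** A QALY total is an area under a utility curve, so the timing of the utility measurements is part of the estimate. Here the first two EQ-5D readings are baseline and the 3-month visit. Everything that happens to utility during the course of therapy and just after it lies between them. If the two points are joined by a straight line, the curve in that interval is fixed by its ends.

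A gain that peaks at the end of therapy and then fades is partly or wholly missed. A gain that holds is treated as if it built up slowly. A gain that comes late is credited too early. The planned economic sensitivity analysis concentrates on the main cost-drivers, so it would not show any of this. No later analysis rule can recover a T1 value that was never measured; it can only assume one. What is at stake is the accuracy of the QALY difference, the denominator of the cost per QALY.

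**Working it through.** The article states no QALY figure, utility gain or interpolation rule, so there is no plan figure to reproduce. The check compares the trapezoidal area with and without a T1 point.

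**Inputs**
- From the article: an 8-week course; T1 one week after it; visits at 3, 6 and 12 months; EQ-5D at T0, T2, T3 and T4.
- Assumed: therapy starts at baseline, so T1 falls at week 9; trapezoidal interpolation; the utility paths below.
- Origin of the months, both readings: weeks 0, 9, 21, 34, 60 (from the end of therapy) or 0, 9, 13, 26, 52 (from baseline).

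**Formula.** Let g1 and g2 be the between-arm utility gains at T1 and T2 (zero at T0), at weeks t1 and t2. Only the T0–T2 segment differs.
- With T1: ½·g1·t1 + ½·(g1 + g2)·(t2 − t1)
- Without T1: ½·g2·t2
- Missed area = with − without = ½·(g1·t2 − g2·t1)

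The gain is understated only if g1/g2 > t1/t2. That threshold is 9/21 = 43% if months run from the end of therapy and 9/13 = 69% if they run from baseline. At exactly the threshold (linear growth to T2) there is no error.

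**Results in utility-weeks**, scaled to a gain of 1 at T1 (at T2 for the delayed path):

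| Assumed gain at T1, T2, T3, T4 | From end of therapy: with / without T1 | Missed | From baseline: with / without T1 | Missed |
|---|---|---|---|---|
| 1, 1, 1, 1 (sustained) | 55.5 / 49.5 | 11% | 47.5 / 45.5 | 4% |
| 1, 0.75, 0.5, 0.25 | 32.9 / 25.8 | 22% | 25.9 / 22.8 | 12% |
| 1, 0.5, 0.5, 0.5 | 33.0 / 24.75 | 25% | 27.0 / 22.75 | 16% |
| 1, 0.5, 0.25, 0 | 21.6 / 13.4 | 38% | 15.6 / 11.4 | 27% |
| 1, 0.5, 0, 0 | 16.75 / 8.5 | 49% | 10.75 / 6.5 | 40% |
| 1, 0, 0, 0 (gone by T2) | 10.5 / 0 | 100% | 6.5 / 0 | 100% |
| 0, 1, 1, 1 (delayed) | 45.0 / 49.5 | −10% (overstated) | 41.0 / 45.5 | −11% (overstated) |

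For example, the sustained gain with months from the end of therapy: with T1, ½·9 + 51 = 55.5; without, ½·21 + 39 = 49.5; missed 6/55.5 = 11%.

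**Absolute size.** With an assumed utility gain of 0.05, the missed amount runs from 2 × 0.05/52 = 0.002 QALY (sustained, from baseline) to 10.5 × 0.05/52 = 0.010 QALY (gone by T2, from the end of therapy). The delayed path overstates by 4.5 × 0.05/52 = 0.004 QALY.

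**The case against.** The schedule is not an error. The text and the table footnote agree, one timetable for all cost-evaluation instruments keeps costs and effects on the same time points, and four utility readings over 12 months can support a cost per QALY. That stands, and it makes this a design improvement and not a contradiction. The straight line is also an inference: an interpolation rule may sit in an analysis plan that is not shown. That stands too, though any rule would have to assume the T1 value.

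A reader might go further and infer that the omission loses the benefit of therapy, understates its QALYs and biases the ICER against MCGP-CS. Taking the path that halves by T2 and then holds, with months from the end of therapy, the ICER would rise by a third (1/0.75 = 1.33). The article does not support this as a general conclusion. It refers only to "the expected improvement in psychological functioning in the MCGP condition" and gives no EQ-5D effect, peak time or decay. Every path that yields a marked understatement places the full gain at T1 by assumption. A delayed effect reverses the sign: the ICER would then look lower (1/1.10 = 0.91). A sustained gain is seen at T2, T3 and T4 and is mostly counted.

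The week-9 placement of T1 is also soft. Baseline precedes randomisation, and randomisation waits until a group has 8 members. If months ran from baseline, a four-week wait would put T1 at week 13, level with T2, and the gap would vanish. The listing of one week and then 3, 6 and 12 months reads more naturally as counted from the end of therapy, but the article does not settle it.

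Finally, early change is not wholly unseen, since the QLQ-C30 is collected at T1. It is not the utility instrument named for the cost-utility analysis.

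**Conclusion.** The point holds as a cheap improvement. The instrument that supplies the QALYs is not given at the assessment closest to the end of therapy, and the resulting interpolation error can run either way. With the full gain at T1, about 4–11% of a sustained gain is missed, and about 12–38% of a gain that fades along the three gradual paths; faster fading loses more, up to all of a gain gone by T2. If nothing has appeared by T1, the gain is overstated by about 10%. Understatement requires a T1 gain above about 43% of the T2 gain (months from the end of therapy) or about 69% (from baseline).

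These figures rest on trapezoidal QALYs, T1 at week 9 and assumed utility paths. In absolute terms the effect is small at an assumed gain of 0.05. A direction of bias, or a definite distortion of the ICER, cannot be claimed.

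**What to change.** - Add the EQ-5D alone, without the TiC-P or PRODISQ, to the T1 questionnaire in all three arms.
- Amend the Outcome assessment text and Table 2 so that the EQ-5D is assessed at T0, T1, T2, T3 and T4, with a footnote separate from that of the cost instruments.
- Compute QALYs as the area under all five points, with adjustment for baseline utility, and state whether follow-up months run from baseline or from the end of therapy.
- For participants already past T1, report a sensitivity analysis with alternative T0–T2 paths. With months from the end of therapy and a T2 gain of g2, the change to the straight-line area is +6·g2 utility-weeks if the T2 value is reached by T1, +16.5·g2 if the T1 gain is twice the T2 gain (½·(2·21 − 9)), and −4.5·g2 if nothing has appeared by T1. With months from baseline, the first is +2·g2, the second +8.5·g2 (½·(2·13 − 9)), and the third is unchanged.

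The cost is a minor amendment and a few more items per participant (about five, assumed). The T1 set already has at least 39 + 21 + 49 + 30 + 14 + 20 + 10 = 183 stated items, plus the MAC. No new visit, staff or procedure is needed.
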